## Abstract

**Background:**

Diarrhea is a common adverse reaction in patients with cancer receiving chemotherapy, for which there is currently no effective method of treatment. Shengjiang Xiexin decoction (SXD), a classic traditional Chinese medicine (TCM) formula, has shown efficacy in alleviating irinotecan-induced diarrhea in preliminary clinical studies. The current study is designed to assess the efficacy and safety of SXD for prophylaxis against irinotecan-induced diarrhea. Additionally, we employ a new approach to analyze and evaluate the data based on the patients’ uridine diphosphate glucuronosyltransferase 1A1 (UGT1A1) genotype, which predicts the risk of diarrhea.

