SXD is recorded in the traditional Chinese medicine (TCM) classic “Treatise on Febrile Diseases” from 2000 years ago. It is typically administered for the treatment of inflammatory bowel disease [14]. In our previous study, we found that SXD significantly reduced irinotecan-induced gastrointestinal toxicity, especially in the presence of the UGT1A1 mutation. It is well-known that toxicity with the mutant type is more serious than with the wild type. However, no significant differences in toxicity were noted between the mutant and the wild type when SXD was administered (*P* > 0.05) [15]. In addition, we established a model of diarrhea in the rat to explore the possible mechanisms of the antidiarrheal action of SXD. We found that treatment with SXD was associated with an inhibitory effect on intestinal apoptosis combined with a promotional effect on intestinal cell proliferation, owing to enhanced maintenance of intestinal stem cells (ISCs) [16]. Another animal study showed that SXD altered the pharmacokinetics of irinotecan and its metabolites to alleviate irinotecan-induced diarrhea, specifically by reducing the hepatic transporters multidrug resistant-associated protein-2 (Mrp-2) and P-glycoprotein (P-gp) and by upregulating UGT1A1 in the liver and jejunum [17].

We designed this study because there have been no large-scale clinical trials and little high-level clinical evidence on the treatment and prevention of CRD. The aim of our study is to evaluate the efficacy and safety of SXD prophylaxis against irinotecan-induced diarrhea in patients with SCLC, specifically that involving the UGT1A1 mutation as determined by genetic analysis before initiating chemotherapy. In this way, we hope to balance the groups by reducing the bias otherwise caused by different levels of risk of CRD in different genotypes. Meanwhile, we will also evaluate whether SXD has an impact on the efficacy of chemotherapy.

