### Sample size

The study proposes that SXD can reduce the occurrence of irinotecan-related diarrhea in patients with SCLC, which was the working hypothesis we used to calculate sample size. This study was designed as a superiority trial and sample size calculations are based on the primary outcome measurement - the incidence and percentage of CRD. Based on the results of our preliminary observational study and previous literature [18], the incidence of CRD is 37.5% (6/16) with SXD and 63.4% without SXD, respectively.

In our study, the ratio of subjects will be 1:1 in both the SXD and control groups. Sample size calculations were performed using PASS software, version 15.0, for a superiority test for two independent, randomized samples. With a significance level of 5% (α), a two-sided test, and power of 80% (1 − β), the required sample size was determined to be approximately 40 per group. Considering an estimated dropout rate of 20%, 50 subjects will be required per group, giving a total of 100 subjects.

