### Randomization and blinding

The relative risk of irinotecan-induced diarrhea for different UGT1A1 gene polymorphisms is wild type (TA6/6) < heterozygous mutant (TA6/7) < homozygous mutant (TA7/7). Based on this, we will perform stratified UGT1A1 genotype randomization. Eligible participants with the UGT1A1 gene will first be stratified into one of two groups - low or moderate-to-high risk of CRD - after which they will be randomized to the SXD cohort or placebo cohort for each level of risk.

Randomization will be implemented by an external agency specializing in the conduct of randomized clinical trials (Beijing Yin Rui Da Medicine Technology Co. Ltd., Beijing, China). The agency will not participate in data management or statistical analysis. Statistical Analysis System (SAS) software, version 9.4, will be utilized to stratify randomization.

The stratified ratio of participants in the low risk (TA6/6) and moderate-to-high risk (TA6/7 and TA7/7) groups will be consistent with the methods used in prior studies. In one previous study, UGT1A1 gene detection in 141 patients with cancer treated with irinotecan showed that the distribution of UGT1A1*28 TA6/6, TA6/7, and TA7/7 genotypes was 74.4% (*n* = 105), 23.4% (*n* = 33), and 2.1% (n = 3), respectively [19]. In a separate study of 2093 Chinese patients from more than 15 hospitals in Shandong, the distribution of the UGT1A1*28 TA6/6, TA6/7 and TA7/7 genotypes was 76.5% (*n* = 1601), 22.1% (*n* = 463) and 1.4% (*n* = 29), respectively [20]. The estimated stratum ratio is therefore determined to be 3:1.

The random sequence will be generated using SAS software with an allocation ratio of 1:1. SXD or placebo will be sealed in an opaque paper box labeled by randomization number and allocated based on that number. The participants will be assigned a randomization number and will receive the corresponding package, containing either SXD or the placebo.

All researchers and participants, excluding the researcher in charge of randomization, will be blinded to the assignment until the trial is completed. Emergency letters will be attached to each labeled box that will be kept by a specially assigned person in each center. If participants have severe AEs, the letters will be opened to reveal the participants’ allocated interventions.

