### Statistical analysis

The study data will be managed and analyzed by an independent biostatistician using SPSS (Statistic Package for Social Science, v20.0). This study includes four data sets for analysis: intention to treat (ITT), per-protocol set (PPS), full analysis set (FAS), and safety set (SS).

ITT analysis will be used to analyze the primary outcome for SXD efficacy in preventing or reducing the incidence and severity of CRD, and will include all study participants. Any missing primary outcome data will be supplemented by carrying forward the last recorded data.

PPS analysis will be performed to test the robustness of the ITT analysis and will only include participants who strictly follow the protocol and finish the study. The results from the two analyses will be considered credible if they are consistent; otherwise, the results will require sufficient discussion and explanation. Furthermore, is compliance is too low, CACE analysis will be implemented to provide an unbiased and robust estimation of treatment effect. The analysis of secondary outcomes will be based on the results of the PPS analysis.

The FAS analysis will include all randomized participants who completed at least one treatment and one follow up. To analyze the intervention-related AEs, the SS analysis will evaluate all safety outcomes for every randomized participant who received any intervention at least once during the study period.

Continuous data will be presented as the mean and standard deviation (SD), and noncontinuous data (including categorical or ranked data) will be presented as count and number (percentage). We will analyze categorical data as the risk ratio (RR) with 95% confidence intervals (CI), and analyze continuous data as mean differences (MD) and their 95% CI.

The incidence of diarrhea, modification rate of the chemotherapy regimen, and incidence of hospitalization are categorical data. The chi-square test or Fisher’s exact test will be conducted to compare the differences in those data between two groups. The Wilcoxon rank sum test will be conducted to evaluate the difference in ranked data between the two groups, which includes the grade of diarrhea and evaluation of chemotherapy efficacy. Repeated-measures analysis of variance (ANOVA) will be used to compare continuous values such as the use of antidiarrheal drugs. In all tests, a *P* value of < 0.05 will be considered statistically significant.

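### Randomization is stratified by UGT1A1 risk group, but the named tests and risk ratio ignore the strata, and the genotype-based evaluation announced in the abstract is absent from the analysis section

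*Protocol article*

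**What the plan says.** **Design.** Under Randomization and blinding the article says "we will perform stratified UGT1A1 genotype randomization". There are two levels, low risk (TA6/6) and moderate-to-high risk (TA6/7 and TA7/7), with an expected ratio of 3:1 and 1:1 allocation to arms.

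**Stated intention.** The abstract's Background says "we employ a new approach to analyze and evaluate the data based on the patients", continuing with their UGT1A1 genotype. In the main Background, the aim refers to diarrhea prophylaxis in these patients, "specifically that involving the UGT1A1 mutation as determined by genetic analysis before initiating chemotherapy".

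**Analysis.** The Statistical analysis section treats incidence of diarrhea, regimen modification and hospitalization as categorical. For these, a chi-square or Fisher's "exact test will be conducted to compare the differences in those data between two groups". Diarrhea grade and chemotherapy efficacy get a two-group Wilcoxon rank sum test. Categorical effects are given as a risk ratio with 95% CI. The section contains no stratified test, genotype covariate, genotype subgroup or treatment-by-genotype term.

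**The concern.** The protocol treats genotype as strongly prognostic. Its Background cites severe diarrhea in 1/78 wild-type, 6/19 heterozygous and 4/6 homozygous patients, and its Discussion cites a meta-analysis with more diarrhea in TA6/7 and TA7/7. Stratifying on such a factor removes its between-stratum variation from the comparison of arms, provided the arms are balanced within strata. A test that pools the strata puts that variation back into the standard error. The rejection rate under the null then falls below the nominal level and the interval is wider than it need be. If the arms are not balanced within strata, the pooled test carries the chance imbalance as noise and loses power. Separately, the abstract announces an evaluation that the analysis section does not provide.

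**Working it through.** **Inputs from the protocol article**
- Sample size section: "With a significance level of 5% (α), a two-sided test"; "the incidence of CRD is 37.5% (6/16) with SXD and 63.4% without SXD, respectively"; 50 per group after 20% dropout.
- Randomization and blinding: strata 3:1, so about 75 and 25 of 100 patients, or 12–13 higher-risk patients per arm.

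**Input not in the article (assumption).** The gap d in any-grade CRD between the two strata is not given. I use d = 0 to 48 points around an overall 63.4%. The ceiling follows from 0.634 + 0.75d ≤ 1, so d ≤ 0.488.

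**The plan's own figure.** The stated "the required sample size was determined to be approximately 40 per group" does not reproduce. The usual two-sided formula gives n = [1.96√(2 × 0.5045 × 0.4955) + 0.8416√(0.375 × 0.625 + 0.634 × 0.366)]² / 0.259² = 3.844 / 0.0671 = 57.3, so 58 per group. Approximate power is 64% at 40 and 74% at 50 per group. That is a separate matter and does not affect the point here, which is worked at 50 per arm.

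**Balanced arms within strata**
- Stratum rates under the null: p_low = 0.634 − 0.25d, p_high = 0.634 + 0.75d.
- Within-stratum variance: W = 0.75 p_low(1 − p_low) + 0.25 p_high(1 − p_high).
- Pooled variance: V = 0.634 × 0.366 = 0.2320. Ratio R = W/V.
- True type I error ≈ 2[1 − Φ(1.96/√R)]. Excess interval width ≈ 1/√R − 1.

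Example, d = 0.48: W = 0.75 × 0.514 × 0.486 + 0.25 × 0.994 × 0.006 = 0.1888, so R = 0.814 and √R = 0.902. Then 1.96/0.902 = 2.172, which gives 0.030. Excess width is 1/0.902 − 1 = 10.8%.

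The simulated columns use 100,000 trials with 38 + 12 patients per arm, chi-square and CMH both without continuity correction. Power uses the planning risk ratio 0.375/0.634 = 0.591 in both strata.

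| Gap d | Null rates, low / higher risk | R | Type I, formula | Type I, unstratified (simulated) | Type I, CMH (simulated) | Interval excess | Power, unstratified / CMH |
|---|---|---|---|---|---|---|---|
| 0 | 63.4% / 63.4% | 1.000 | 5.0% | 5.1% | 5.1% | 0% | 76.3% / 76.3% |
| 20 | 58.4% / 78.4% | 0.968 | 4.6% | 4.6% | 4.8% | 1.7% | 76.2% / 76.2% |
| 30 | 55.9% / 85.9% | 0.927 | 4.2% | 4.2% | 4.8% | 3.8% | 76.4% / 76.5% |
| 40 | 53.4% / 93.4% | 0.871 | 3.6% | 3.5% | 5.2% | 7.2% | 76.7% / 77.2% |
| 48 | 51.4% / 99.4% | 0.814 | 3.0% | 3.0% | 5.1% | 10.8% | 77.2% / 78.5% |

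**Arms not balanced within strata** (simple 1:1 randomization inside each stratum, 200,000 trials)
- Null rates assumed at 55% and 88.6%: unstratified type I error is about 5.2%, so the conservatism is gone.
- A strongly separated alternative (assumed: control 50% and 95%, SXD 25% and 75%): power is 67.4% unstratified against 74.5% CMH, a gap of 7.1 points.
- The same alternative with 12 higher-risk patients in each arm gives 70.7% against 75.2%. With 13 in control and 12 in SXD it gives 74.3% against 75.1%. So the gap depends on the alternative and on single patients in the small stratum, as well as on imbalance.

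**Precision by genotype.** With about 12.5 higher-risk patients per arm, power at the planning rates within that stratum is about 25%. Any genotype comparison can only be exploratory.

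**The case against.** **The test is not anti-conservative.** True. In every scenario its type I error is close to or below 5%. A reader might infer that a positive result would be unsafe; nothing here supports that.

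**Conservatism depends on blocking, which is not stated.** This stands, and both cases are shown for that reason. An article may leave block details to the full protocol, so the omission is no fault in itself.

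**The effect on the primary outcome is small and rests on an assumed gap.** This also stands. At gaps of 20 points or less the change is under half a percentage point of type I error. If genotype hardly predicts any-grade CRD and allocation is unblocked, the stratified test may even have slightly less power.

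**The severe-diarrhea rates make the problem look larger.** A reader might apply the unstratified chi-square to 1.28% against 40% (10/25 carriers) and find a much stronger distortion. The plan contains no binary test of severe diarrhea: severity enters as ranked grade. Those rates show that genotype is prognostic; they do not size the error of a planned test.

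**Genotype is there only to balance the groups.** The Background, after stating the aim, and the Discussion both say so, and no genotype-by-treatment outcome is listed. A reader might infer that the trial leaves a declared genotype objective unanswered. The documents do not support that much: the suggestion rests chiefly on the abstract's wording. Nor does the article plan to argue from separate P values by genotype. The earlier study in the Background compared mutant with wild type among patients given SXD.

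**The analysis plan may deal with it.** Silence could be left to that document. Here the article names specific unstratified tests, and an analysis plan written to match would repeat the mismatch.

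**Conclusion.** The point holds in a limited form. The analysis named for the primary and ranked outcomes does not follow the stratified randomization, and the abstract announces a genotype-based evaluation that the analysis section lacks.

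With arms balanced within strata, the cost is mild conservatism (type I error 5.1% down to 3.0% over assumed gaps of 0 to 48 points), intervals about 0–11% too wide, and about 0–1 point of power at the planning risk ratio. Without balance, type I error stays near 5%, and the loss of power reaches about 7 points only in a strongly separated example.

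These sizes rest on 50 per arm, 3:1 strata and assumed any-grade stratum rates. The ranked-outcome tests were not simulated; for them the argument is one of principle. The change is worth making because it is nearly free, and validity of the trial does not hang on it.

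**What to change.** - **Primary outcome:** a CMH test stratified by UGT1A1 risk group, with a Mantel-Haenszel risk ratio and 95% CI. Use the same for regimen modification and hospitalization.
- **Ranked outcomes:** a van Elteren (stratified Wilcoxon) test for diarrhea grade and tumour response.
- **Genotype statement, one of two:** either report the treatment effect in each stratum with a treatment-by-genotype interaction estimate and CI, labelled exploratory given 12–13 higher-risk patients per arm; or reword the abstract to say that genotype is used only to balance the arms.
- **For the reader's benefit:** state whether allocation within strata is blocked, since that decides which of the two cases above applies.

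The cost is analysis wording only: no extra patients, visits or data, because genotype is already known for everyone randomized. It should be settled before unblinding.

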## Discussion

Diarrhea induced by chemotherapy can affect the design and completion of chemotherapy regimens, lower the quality of life in patients with cancer, and increase medical expenses [24]. Loperamide and octreotide are currently recommended to treat CRD, as recommended by expert consensus. However, the effect of loperamide is limited [11], and there is a risk of cardiac arrhythmia when the dose and frequency are too high [12, 13]. Octreotide is not reliably effective in treating CRD. Additionally, there is currently no recommended means of preventing diarrhea. It is therefore necessary to develop an effective method of preventing or reducing the incidence of CRD that does not have significant adverse side effects. Traditional Chinese herbal medicine has recently gained more attentions for its potential to prevent or treat chemotherapy-induced adverse events [25].

Several classic TCM prescriptions have been shown to have some efficacy in treating or preventing irinotecan-induced diarrhea. For example, Banxia Xiexin decoction was shown to relieve or control diarrhea in patients with recurrent SCLC undergoing irinotecan-based chemotherapy [26]. Another Chinese herbal compound, Huangqin decoction (PHY906), was also found to reduce the incidence of irinotecan-induced diarrhea and decrease the use of loperamide [27]. In one of our previous studies in which oral SXD was administered as adjuvant therapy, the incidence of irinotecan-induced diarrhea in patients with UGT1A1 mutation was found to be nearly equal to that of patients with the wild-type mutation [15].. This effect was more notable among patients with a UGT1A1 mutation who were considered to be at high risk of developing CRD. Therefore, for this study, we included the UGT1A1 gene as a stratified random factor to balance the study groups.

The UGT1A1 polymorphism has a significant relationship with irinotecan-induced toxicity, including both diarrhea and neutropenia [28]. The common main gene mutations are UGT1A1*28 and UGT1A1*6; however, both remain controversial in regard to clinical guidance. A meta-analysis involving 58 studies and 6087 patients has demonstrated the predictive value of UGT1A1*28: patients with TA6/7 and TA7/7 genotypes had a higher incidence of diarrhea and neutropenia than those with the TA6/6 genotype [29]. Other studies found that the UGT1A1*6 polymorphism was associated with a higher risk of severe diarrhea [20, 30]. The differences in the findings of these studies might be due to the discrepancy in irinotecan dose, the type of tumor, and patient age. Another study analyzed both UGT1A1*6 and *28 gene polymorphisms and found that UGT1A1*6 plays a more vital role in hematologic toxicity, whereas UGT1A1*28 is more involved in the development of diarrhea [9]. In addition, compared with western populations, UGT1A1*6 mutations are more common than UGT1A1*28 mutations in Chinese populations [31]. Because UGT1A1*28 polymorphisms have higher specificity, we designed our current study to use UGT1A1*28 as the stratification factor for balancing the groups. Future studies that include both the UGT1A1*28 and UGT1A1*6 polymorphisms may provide a more accurate predictive result.

The time to onset of CRD depends on the drug and schedule. The median time to onset of irinotecan-induced late diarrhea is about 6 days with the 3-week, 350 mg/m^2^ dose. For the weekly schedule and 125 mg/m^2^ dose, the median time to onset is 11 days [4]. Objective tumor response is typically evaluated every two cycles. Thus, we designed this study to encompass two complete chemotherapy cycles.

Previous studies have mainly used the CTCAE diarrhea grading system to evaluate CRD. Because this system only focuses on the frequency of diarrhea, but not duration or concomitant symptoms such as stomachache, abdominal distension, and cramps, it cannot provide a complete assessment of reported incidents of CRD. To address this issue, our study will require each participant to record a detailed diary of all aspects of their diarrhea.

More evidence is needed to determine whether adjuvant therapy with Chinese herbal medicine alters the chemotherapy response. Thus, we have chosen to evaluate chemotherapy efficacy as a secondary outcome in this study.

Finally, we have included testing for the UGT1A1 gene as a means of randomly stratifying groups to balance the groups before they are randomized to treatment or control. This measure could thereby reduce bias in evaluating the efficacy of SXD as prophylaxis for irinotecan-induced diarrhea. The results of this study should help to generate high-level clinical evidence for this Chinese herbal compound as a means of preventing or decreasing the incidence of CRD.

## Data Availability

Not applicable.

## Abbreviations

ADL: Activities of daily living
AEs: Adverse events
CFDA: China Food and Drug Administration
CRA: Clinical research associate
CRD: Chemotherapy-related diarrhea
CRA: Clinical research associate
CRF: Case report form
CT: Computed tomography
CTCAE: Common Terminology Criteria for Adverse Events
ECOG: Eastern Cooperative Oncology Group
FAS: Full analysis set
GMP: Good Manufacturing Practice
ISCs: Intestinal stem cells
ITT: Intention to treat
MRI: Magnetic resonance imaging
NCCN: National Comprehensive Cancer Network
NCI: National Cancer Institute
PCR: Polymerase chain reaction
PI: Principal investigator
PPS: Per-protocol set
RECIST: Response Evaluation Criteria in Solid Tumors
SCLC: Small cell lung cancer
SPSS: Statistic Package for Social Science
SS: Safety set
SXD: Shengjiang Xiexin decoction
ULN: Upper limit of normal
